**Assessments**									
Laboratory tests		√					√		
Muscle action time, EMG data		√					√		
JOA, MPQ		√					√	√	√
Adverse events				√	√	√		√	√
Safety evaluation							√	√	√

### Inclusion criteria

Eligible participants who met the following criteria will be included: (i) pain between the costal margin and inferior gluteal fold for at least 12 weeks which is not caused by a specific pathology, (ii) age between 20 and 39 years old, (iii) never received drug treatment, non-pharmacy, or surgical treatments for CNLBP during the previous 12 weeks, and (iv) agree to join the study and sign the written informed consent.

### Exclusion criteria

Participants matching any of the following criteria will be excluded: (i) LBP with a specific diagnosis such as lumbar disc herniation, fracture of lumbar vertebra, spinal stenosis, severe osteoarthritis, or ankylosing spondylitis, (ii) be suffering from serious diseases of the heart, liver, kidney, or other organs, (iii) pregnant women, tumor patients, or those with serious disorders, (iv) structural deformity of the lumbar spine, (v) be suffering from other diseases that cause pain, such as migraine, angina, etc., and (vi) patients received surgery, acupuncture, massage, Tuina, spinal manipulation, and NSAIDs treatment in the past 12 weeks.

### Interventions

#### Mawangdui-Guidance Qigong Exercise therapy

For a session of 4 weeks, participants in the experimental group will receive Mawangdui-Guidance Qigong Exercise therapy five times each week. Each exercise will continue for 30 min and be led by a particular coach who is equally skilled and experienced and has received training in how to manage a project. Figure 2, Table 2, and Supplementary video 1 show the program of the Mawangdui-Guidance Qigong Exercise’s “yinyao” movement.

**FIGURE 2 F2:**
[figure not shown]
The action of the Mawangdui-Guidance Qigong Exercise’s “yinyao” movement.

**TABLE 2 T2:** The steps of the Mawangdui-Guidance Qigong Exercise’s “yinyao” movement training.

i	Relaxed standing, both hands staying at palm, move both palms from abdomen to waist along Belt Vessel with hands sticking to it; palms brace against waist and push it ahead to the body leaned forward.
ii	Both palms move downward to hip and turn body bended, keep moving palms along the back of thighs and shins to heel and moving palms from heel to forward, hanging the arms and palms upon the tiptoes, rise head and look straight ahead.
iii	With the last posture referred in (ii), rotate the waist and lift the left shoulder and palm at the same time, meanwhile, turn the head backward and look to left rear.
iv	Rotate the waist and droop the left shoulder, meanwhile, turn back the head and look to infra-anterior.
v	Lift the body upright as well as the palms lift to the chest with it rotating interior and back of the palms being against to each other along the anterior median line, and look straight ahead.
vi	Move both palms to belly, and move them from abdomen to waist along Belt Vessel with hands sticking to it; palms brace against waist and push it ahead to the body leaned forward.

The main movement is the same as ii–v, except for the rotation of head, waist, and shoulder turns to right. Both palms fall at both sides until the second movement terminated and look straight forward.

#### Motor control exercise

The main goal of these exercises in the MCE group is to normalize the significant motor abnormalities by teaching participants to maintain stable posture while properly contracting their muscles to lessen pain and intensity. Precious study helps to set the MCE strategy (Li et al., 2021). Participants will practice five times a week for 30 min each under the guidance of a specified experienced physiotherapist. Table 3 depicts the MCE process steps.

**TABLE 3 T3:** The steps of motor control exercise.

i	In the first step, the participants’ ability to control the joint neutral position in the four-point kneeling position will be retrained. The participants learned how to find their postural balance in the basic training.
ii	In the second step, the participants will learn how to control movements in their lumbar spine with minimal effort while moving their arms and legs. Participants will be asked to lift one limb to a horizontal position for 5 s during four-point kneeling. Each limb will be repeated thrice with a break of 15 s.
iii	In the third step, the participants will lift one arm and the contralateral leg to a horizontal position for 5 s. This action will also be repeated three times with a break of 15 s.

#### Drug treatment

A qualified and experienced doctor who has received the same training as the medicine group will evaluated and give oral celecoxib (Celebrex, Pfizer), 200 mg once daily, for 4 weeks to participant. The doctor will provide drug counseling throughout the duration of the experiment, as well.

To guarantee impartiality and rigor, participants with increased muscle pain after exercise and no obvious relief after rest will be treated with appropriate cryotherapy under the supervision of researchers. However, additional treatments including decoction, Chinese herbs, acupuncture, Tuina, and other painkillers will not be permitted.

### Outcome measures

#### Primary outcomes

Primary outcomes include muscle activation sequence (Hodges, 2001; Suehiro et al., 2015), iEMG, RMS, and MF, generated from sEMG (Thomas et al., 2007; Aruin et al., 2015; Aruin, 2016). The EMG data will be gathered from the probe on the surface of deltoids, lumbar multifidus, transverse abdominis muscle (TrA), erector spinae muscle, gluteus maximus, and hamstrings. Each channel’s interelectrode distance will be 10 mm.

#### Secondary outcomes

The JOA Score (Oshima et al., 2020) and the McGill Pain Questionnaire (MPQ) (Main, 2016) are the secondary outcomes. JOA Score takes into account bladder function, daily activity, clinical indicators and subjective complaints, with the lowest score of 6 and the highest score of 29. Better functioning conditions are indicated by higher overall scores. MPQ is made up of 15 carefully chosen words, comprising 4 emotional and 11 sensory words. Each item is given a number from 0 to 3, with a higher score denotes a severer symptom (Choi et al., 2015). Biomarkers like substance P (Bhatia, 2015) and beta-endorphin (Choi and Lee, 2019) will also be tested.

All the primary and secondary outcomes will be assessed before and 1 week after treatment.

#### Adverse events

Researchers will keep track of adverse events and evaluate the correlation with therapies. Once relevant severe adverse event occurs (major damage to the heart, liver, kidneys, or other organs), the researchers will evaluate the participant can continue this trial or not. If serious adverse reactions occur, visits will continue after safety and treatment after the patient’s trial is suspended.

### Sample size

By utilizing a two-sided 0.05 level *t*-test with >95% power and assuming a 10% dropout rate, the sample size was estimated to demonstrate the influence of the target muscles on MF (Zhou, 2018). To detect a target effect size of 0.44 (GPower 3.1) with 28 participants in each group, a sample size of 84 participants is needed.

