### Statistical analysis

Test-retest reliability and content consistency reliability will be used to gauge the scale’s dependability (test-retest reliability). Cronbach’s coefficient is the most often used measure of internal consistency reliability. The better the homogeneity, the higher the Cronbach’s alpha coefficient. If the scale’s consistency is greater than 0.8, it is considered to be good, and if it is greater than 0.7, it is considered to be acceptable.

SPSS version 20.0 (SPSS Inc., Chicago, IL, USA) will be used for all of the analysis. The significance threshold will be set at 0.05, and the confidence interval will be 95%. The χ^2^ will be used to analyze categorical data. For continuous variables, mean ± SD will be recorded by using ANOVA test if they were normally distributed, or the median with interquartile range will be shown with Kruskal–Wallis H test. The Bonferroni correction and Tukey *post-hoc* test (for ANOVA) will be used to handle multiple comparisons (for Kruskal–Wallis). The Chi-square test will be used to verify the classification count data. Two-tailed test will be used in this study. The difference will be regarded as statistically significant when *P* < 0.05.

To handle missing data, we will evaluate the underlying cause, employ an imputation adjustment approach, and do a last observation carried forward analysis. Following the primary analysis, a sensitivity analysis will be carried out to determine the effect of missing data on the trial outcomes by contrasting the findings from the per-protocol analysis and the intention to treat analysis. Also planned are subgroup analysis by the center.

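### The sample-size statement does not fit together: the t-test it names cannot give more than 95% power at effect size 0.44 with 28 per group, and 84 leaves no room for the stated 10% dropout

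*Protocol article*

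**What the plan says.** The Sample size section bases the calculation on the median frequency (MF) of the target muscles. It names a "two-sided 0.05 level *t*-test with >95% power", adds that it is "assuming a 10% dropout rate", and ends: "To detect a target effect size of 0.44 (GPower 3.1) with 28 participants in each group, a sample size of 84 participants is needed". It does not say whether the t-test is two-sample or paired, or whether 0.44 is a standardised mean difference (Cohen's d) or an ANOVA effect size (Cohen's f).

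The Allocation section randomises 28 participants to each of three arms, 1:1:1. For continuous variables the Statistical analysis section plans that "mean ± SD will be recorded by using ANOVA test if they were normally distributed", with Kruskal–Wallis otherwise, and mentions Tukey and Bonferroni for multiple comparisons. It plans no t-test.

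**The concern.** The section gives every element of a power calculation except the effect-size metric, so it can be checked. An effect size quoted beside a t-test is naturally read as a difference in standard deviations between two groups. On that reading 28 per group falls far short of 95% power. The named test also disagrees with the planned three-group analysis.

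What is at stake is how the MF results are read. The trial compares Qigong with motor control exercise and with celecoxib, and both are pairwise comparisons. A reader who believes that the trial had more than 95% power for a 0.44 SD difference would give a non-significant pairwise MF result more weight than it can bear.

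**Working it through.** **Inputs (Sample size section):** alpha 0.05 two-sided; power above 95%; effect size 0.44, metric not stated; 28 per group; total 84; dropout 10%. Three equal groups (Allocation section).

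**1. The calculation as named: two-sample t-test, 0.44 read as Cohen's d.**
Noncentrality = d × √(n/2), with 2n − 2 degrees of freedom.
- n = 28: 0.44 × √14 = 1.646; df 54; critical t = 2.005; power **36.6%**.
- n = 25 (28 × 0.9 = 25.2): 0.44 × √12.5 = 1.556; df 48; critical t = 2.011; power **33.2%**.
- For 95% power: n = 135 gives 94.97% and n = 136 gives 95.1%, so **136 per group** is needed. That is 3 × 136 = 408 in total before dropout.

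**2. Other t-test readings, at 28 per group.**

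| Reading | Power |
|---|---|
| Two-sample, one-sided | 49.2% |
| Two-sample, Bonferroni for three pairs | 21.4% |
| Paired, two-sided | 61.2% |
| Paired, one-sided | 73.4% |
| Two-sample, d = 2f = 0.88 | 89.9% |

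None reaches 95%.

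**3. The calculation that reproduces 84: three-group one-way ANOVA, 0.44 read as Cohen's f.**
Noncentrality = N × f², with 2 and N − 3 degrees of freedom.
- N = 84: 84 × 0.1936 = 16.26; critical F = 3.109; power **95.3%**.
- N = 81: 81 × 0.1936 = 15.68; power 94.5%.

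So 84 is the smallest balanced total that reaches 95%, and it contains no dropout allowance.

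**4. Dropout on the ANOVA reading.**
Completers: 84 × 0.9 = 75.6.
- N = 75: power 92.7%.
- N = 76: power 93.0%.

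Keeping 84 completers would need 84/0.9 = 93.3, so 94, or 96 with equal groups.

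**5. What f = 0.44 means between two arms.**
- Means equally spaced: largest difference = f × √6 = 0.44 × 2.449 = **1.08 SD**.
- Two means equal and one different: largest difference = f × 3/√2 = 0.44 × 2.121 = **0.93 SD**.

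**6. Pairwise power for MF at a true difference of 0.44 SD, 28 per arm.**
- Unadjusted: 36.6%, from step 1.
- Tukey, three groups, df 81, critical t = 2.388: **23.5%** (20.8% at 25 per arm).

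Under Tukey at 28 per arm, power is 86% at 0.93 SD and 95% at 1.08 SD.

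**The case against.** The strongest reply is that only the label is wrong. The article never says that 0.44 is Cohen's d. The match with an ANOVA at f = 0.44 is exact, and it fits both the three-arm design and the planned analysis. On that reading the sample does give about 95% power for the omnibus test if everyone completes, and the loss after dropout is about two percentage points. This stands. A reader might infer from the word t-test that the trial really has 37% power instead of 95%. The documents do not support that as a flat statement, because it depends on a metric that they do not give.

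The reply does not remove the point. The named test cannot produce the stated result, and the dropout said to be assumed is not in the 84.

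Two further limits are fair. First, the calculation concerns MF only. The expectation that Qigong does as well as or better than the other arms concerns pain and lumbar function, whose scales are secondary outcomes. The pairwise figures above therefore do not measure power for that clinical claim. Second, the sentence on multiple comparisons is garbled about which correction goes with which test, so Tukey after ANOVA is an inference.

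**Conclusion.** The sample-size statement is wrong as written. No t-test reading tried gives more than 95% power at 0.44 with 28 per group; the most direct one gives 36.6%, or 33.2% after dropout. The best-supported explanation is a three-group ANOVA with f = 0.44 that was mislabelled as a t-test. It then has 95.3% power with all 84 completing and about 93% after 10% loss. Power above 95% with 10% dropout is met on neither reading, but the size of the shortfall depends on the metric: about two points under ANOVA, about 60 points under Cohen's d.

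The ANOVA reading is inferred from a numerical match and from the planned analysis. The source study for the effect size is not at hand, so only the sponsor can confirm it. All figures assume normal outcomes with equal variances, equal arms and dropout spread evenly.

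**What to change.** 1. The sponsor confirms which test and which effect-size metric were used.
2. If it was the ANOVA: replace the t-test wording with a three-group one-way ANOVA of MF, alpha 0.05, Cohen's f = 0.44. Give power as 95.3% with all 84 completing and about 93% after 10% dropout.
3. In that case, state also that f = 0.44 implies a largest pairwise difference of about 0.93 to 1.08 SD, and that pairwise power for MF at 0.44 SD is about 37% unadjusted and about 24% with Tukey at 28 per arm.
4. If 0.44 was meant as Cohen's d in a two-sample t-test: restate power as about 37%, and 33% after dropout.

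The cost is the rewording of one short section, with no change in enrolment. The disclosed power becomes less favourable.

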### Participants recruitment

Chronic non-specific low back pain is an exclusionary diagnosis. Patients with chronic LBP who do not have particular illnesses will be given this diagnosis (Koes et al., 2006). Eligible patients will be recruited from the Department of Orthopedics of Chengdu University of Traditional Chinese Medicine (CDUTCM). To ensure that recruitment messages are easily received by patients interested in the trial, recruitment posters and leaflets are placed in hospital lobbies and orthopedic clinics. Patients can also contact the staff through WeChat and the hospital website to sign up for the trial. In order to improve compliance, participants will be fully informed before signing informed consent. Researchers will keep track of participants’ compliance, including monitoring drug use and exercise on a regular basis. The participant recruiting process started on 23 October 2022, is still running, and it should be finished by 31 December 2022.

### Allocation

Eligible patients will be randomly assigned to the Qigong group (*n* = 28), the MCE group (*n* = 28), or the medication group (*n* = 28) according to the inclusion and exclusion criteria with a ratio of 1:1:1. Prior to intervention, each patient will receive a random number in a sealed envelope. An automated random number generator created this random number, which is specific to each row in the table. A randomizer will assign patients to the experimental or control groups. An assessor who is unrelated to the study will maintain absolute confidentiality regarding the allocation list.

### Blinding

In this study, a single blind approach will be used to execute the Mawangdui-Guidance Qigong Exercise. It is impossible to blind participants and researchers to the group assignment. The same unbiased, skilled evaluators who are blind to the allocation will measure each result.

### Data collecting and monitoring

The Data Monitoring Committee (DMC) for Medical Data in this project is the Chengdu University of Traditional Chinese Medicine Evidence-based Medicine Center. Designated outcome assessors will record data on paper and computerized CRFs, and the DMC will keep an eye on it. Every 3 months, monitors will audit the data. During the evaluation process, coaches and statisticians will not have access to these data.

### Statistical analysis

Test-retest reliability and content consistency reliability will be used to gauge the scale’s dependability (test-retest reliability). Cronbach’s coefficient is the most often used measure of internal consistency reliability. The better the homogeneity, the higher the Cronbach’s alpha coefficient. If the scale’s consistency is greater than 0.8, it is considered to be good, and if it is greater than 0.7, it is considered to be acceptable.

SPSS version 20.0 (SPSS Inc., Chicago, IL, USA) will be used for all of the analysis. The significance threshold will be set at 0.05, and the confidence interval will be 95%. The χ^2^ will be used to analyze categorical data. For continuous variables, mean ± SD will be recorded by using ANOVA test if they were normally distributed, or the median with interquartile range will be shown with Kruskal–Wallis H test. The Bonferroni correction and Tukey *post-hoc* test (for ANOVA) will be used to handle multiple comparisons (for Kruskal–Wallis). The Chi-square test will be used to verify the classification count data. Two-tailed test will be used in this study. The difference will be regarded as statistically significant when *P* < 0.05.

To handle missing data, we will evaluate the underlying cause, employ an imputation adjustment approach, and do a last observation carried forward analysis. Following the primary analysis, a sensitivity analysis will be carried out to determine the effect of missing data on the trial outcomes by contrasting the findings from the per-protocol analysis and the intention to treat analysis. Also planned are subgroup analysis by the center.

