In order to assess internal and external postural interference in patients with LBP, the quick arm raise test and the falling ball test by surface electromyograph (sEMG) are frequently utilized (Hodges and Richardson, 1996; Tsao and Hodges, 2008; Jacobs et al., 2017; Xie and Wang, 2019; Larivière and Preuss, 2021; Yu et al., 2021). Although no consensus was established, numerous EMG studies attempted to shed light on the CNLBP with muscle activity sequence mechanism (Geisser et al., 2005; Marshall and Murphy, 2008; Falla and Hodges, 2017). The influence of adjusting posture on pain reduction and disability improvement may be observed by using EMG to examine the changes in muscle initiation time and iEMGs in patients with CNLBP (Yu et al., 2021). The management of spinal postural alignment and overall body balance are thought to depend mostly on the back muscles (Daggfeldt and Thorstensson, 2003; Christophy et al., 2012). The Chinese Association for the Study of Pain (Ma et al., 2019) advises sEMG y as an objective method of assessing the back muscles’ functionality (Akbari et al., 2015).

There is not enough solid evidence to support the high efficacy of Qigong when compared to other various nonoperative treatments. Mawangdui-Guidance Qigong Exercise has not been subjected to a randomized controlled trial (RCT) to determine the effectiveness in treating CNLBP. We strive to confirm the critical function in treating chronic CNLBP by contrasting Mawangdui-Guidance Qigong Exercise with MCE and medication.

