## Methods and design

### Study design

This study is a randomized, single-blinded clinical trial to investigate the effectiveness of Mawangdui-Guidance Qigong Exercise for CNLBP. This study will be conducted at the Hospital of Chengdu University of Traditional Chinese Medicine (CDUTCM). For the duration of the 4-week course of therapy, 84 participants who meet the trial criteria will be assigned at random to the Mawangdui-Guidance Qigong Exercise group, the MCE group, or the medicine group. Participants in Qigong group and MCE group will receive different types of exercise therapies under the supervision of different professional coaches. Others in the medicine group will be given celecoxib orally on a regular basis. EMG data, including muscle activation time, iEMGs, root mean square value (RMS) and median frequency (MF), will be the main outcomes. The Japanese Orthopedic Association (JOA) Score, the Mcgill Pain Questionnaire (MPQ), beta-endorphin, and substance P will be the secondary outcomes. All outcomes will be evaluated at the start of treatment and 4 weeks later. We think Mawangdui-Guidance Qigong Exercise can produce an improvement in pain and lumbar function that is equal to or greater than what the other two groups can.

The study is approved by the Sichuan Regional Ethics Review Committee on Traditional Chinese Medicine (Approval No. 2020KL-067) and registered with China Clinical Trial Center Registration (ChiCTR2000041080). The implementation follows the principles of the Declaration of Helsinki (Version Edinburgh 2000). The SPIRIT guidelines and CONSORT flow diagram will be followed in this investigation. The whole study design will be illustrated as a flow chart in Figure 1 and the process timetable will be shown in Table 1.

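### The planned pairwise testing spends error on MCE versus celecoxib, which is not an objective; two planned Qigong contrasts would be modestly more powerful (minor)

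*Protocol article*

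**What the plan says.** All references are to the Protocol article; no separate analysis plan is shown.

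- **Question.** The Introduction sets the aim as assessing Qigong "by contrasting Mawangdui-Guidance Qigong Exercise with MCE and medication". Study design gives the hypothesis that Qigong improves pain and lumbar function to a degree "equal to or greater than what the other two groups can". The Discussion repeats this hypothesis and closes on the same two comparisons. MCE versus celecoxib is not posed as a question anywhere.
- **Analysis.** Under Statistical analysis: "For continuous variables, mean ± SD will be recorded by using ANOVA test if they were normally distributed", with Kruskal–Wallis otherwise. Multiple comparisons are handled by Bonferroni and Tukey. I read this as Tukey after ANOVA and Bonferroni after Kruskal–Wallis; the labels in that sentence are not clear, and the number of Bonferroni comparisons is not given.
- **Threshold.** "The significance threshold will be set at 0.05, and the confidence interval will be 95" per cent. Later in the same section: "The difference will be regarded as statistically significant when" P is below 0.05. Neither sentence refers to a particular arm contrast.
- **Size.** The Sample size section gives 28 per arm, 84 in all, from a two-sided 0.05 t-test "with >95% power", an effect size of 0.44 and 10% dropout. It does not say which arm pair the 0.44 refers to, or whether it is Cohen's d or f.

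**The concern.** The question involves two contrasts that share one arm. The stated analysis is built for a different family: an omnibus test over three arms, then comparisons that, with Tukey, cover all three pairs by construction. The third pair, MCE versus celecoxib, takes part of the 5% error allowance and raises the critical value for the two contrasts that the trial is about.

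At stake is some power on the Qigong contrasts, in a trial of only 28 per arm. There is also a matter of interpretation. A difference from celecoxib only, from MCE only, or from both supports different conclusions. Naming the two contrasts in advance, and tying each claim to its own comparator, settles this before the data are seen. The point concerns the arm contrasts within any one outcome and would remain with a single primary outcome.

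**Working it through.** **Inputs from the article.** Three arms, 28 each, 1:1:1; two-sided alpha 0.05; effect size 0.44; power above 95%; 10% dropout.

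**Inputs assumed.** Normal data with a common SD, and the pattern of arm means, since the article gives neither means nor SD.

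**Step 1: the plan's own figure.** Read as a two-sample t-test with d = 0.44, 28 per arm gives 36.6% power, and 95% needs about 135 per arm. This reading does not reproduce 84. A one-way ANOVA with f = 0.44 and three groups does:

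- noncentrality = f² × N = 0.44² × 84 = 16.26
- degrees of freedom 2 and 81, critical F = 3.11, power 95.3%
- at N = 81, power is 94.5%, so 84 is the smallest equal-arm total that reaches 95%

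I therefore use f = 0.44 to set the scale. It is an inference from the arithmetic. How the sample size was derived is a separate matter.

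**Step 2: turn f into a contrast.** If Qigong differs from both comparators by the same amount a and the comparators are equal, f = a√2/3. So a = 0.44 × 3/√2 = 0.933 SD.

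**Step 3: critical values for |t|, 81 df.**

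- Tukey, three pairs: 3.3765/√2 = 2.388
- Dunnett, two contrasts against Qigong: 2.25
- Bonferroni over two contrasts: 2.284; over three: 2.445

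**Step 4: power for one Qigong contrast.** Noncentral t with noncentrality d√(n/2) = d√14. At d = 0.933 this is 3.49, which gives 86.3% with Tukey and about 89.1% with Dunnett. Across other effect sizes, 28 per arm:

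| d | Tukey (3 pairs) | Bonferroni (2) | Dunnett (2) | Dunnett minus Tukey |
|---|---|---|---|---|
| 0.44 | 23.5% | 26.8% | 27.9% | 4.4 points |
| 0.70 | 59.3% | 63.2% | 64.5% | 5.2 points |
| 0.88 | 81.5% | 84.1% | 84.9% | 3.4 points |
| 0.93 | 86.0% | 88.2% | 88.8% | 2.8 points |

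Limiting the family to the two Qigong contrasts thus gains about 2 to 5 points per contrast, depending on the effect size and on which two-contrast method is used. With 25 per arm (28 × 0.9 = 25.2) and d = 0.70, power rises from 53.5% with Tukey to 58.9% with Dunnett.

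**Step 5: power for both Qigong contrasts together.** By simulation with Qigong 0.933 SD from both comparators: about 78% with Tukey and 82% with Dunnett.

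**Step 6: does the planned analysis show where a difference lies?** Take the least favourable layout at f = 0.44: Qigong midway between comparators that are 2 × 0.539 = 1.08 SD apart. By simulation the omnibus test is significant in 95% of trials. In 30.0% of trials it is significant while neither Qigong contrast passes Tukey. In 29.6% Tukey also identifies MCE versus celecoxib as the pair that differs. Where Qigong differs equally from both arms, an omnibus result with neither Qigong contrast occurs in only 0.8%.

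**The case against.** An omnibus test followed by corrected pairwise comparisons is a standard and valid three-arm analysis. Tukey holds the family-wise error at 5% over all pairs, the Qigong pairs included. Preferring Dunnett is a matter of efficiency, and the gain is small. The article is also a condensed document, and naming confirmatory contrasts and a success rule is often left to the full protocol or the analysis plan. Every power figure depends on reading 0.44 as Cohen's f and on a chosen pattern of means. All of this stands, and it keeps the point minor. What remains is that the article does state a procedure, and for normal data that procedure covers a pair that the trial does not ask about.

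A reader might go further and infer that the plan would declare success on a significant omnibus P produced by MCE versus celecoxib alone. The text does not support that. The 0.05 threshold is a general one, in a section that also covers chi-square and post-hoc tests, and nothing makes the omnibus P decisive. Step 6 shows that the planned Tukey comparisons would nearly always reveal such a case. Nor is there an uncontrolled error rate to report, since corrections are planned.

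It can also be said that superiority contrasts do not answer the whole hypothesis. That is correct. Neither Tukey nor Dunnett by itself supports the claim that Qigong is equal to the other arms.

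**Conclusion.** The point holds as a minor, inexpensive improvement. The stated aim involves two Qigong contrasts, while the Tukey procedure spreads error over three pairs. With 28 per arm and Qigong 0.93 SD from both comparators, the cost is about 3 points of power per contrast (86% versus 89%) and about 4 points for both (78% versus 82%). These figures assume f = 0.44, normal data, a common SD and no loss of participants. For the non-normal case the cost cannot be fixed, because the number of Bonferroni comparisons is not stated. The planned analysis is valid, and the documents do not show that it would credit Qigong with a difference between the other two arms.

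**What to change.** In Statistical analysis, before outcome data are analysed:

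1. Name Qigong versus MCE and Qigong versus celecoxib as the two planned contrasts for each outcome tested.
2. For normal data, test them with Dunnett's procedure, Qigong as the reference arm, at a two-sided family-wise 0.05. For non-normal data, use two rank-based contrasts with Holm's adjustment.
3. State that a claim is made only against the comparator whose adjusted contrast is significant.
4. Report the omnibus P and MCE versus celecoxib as descriptive.

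The change is to wording only and needs no further participants or data. Its cost is that MCE versus celecoxib loses confirmatory status, which the stated objectives do not require. It does not supply a basis for concluding that Qigong is equal to a comparator; that part of the hypothesis needs its own margin and analysis.

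### Continuous outcomes are to be compared by ANOVA or Kruskal–Wallis with no baseline covariate, although every outcome has a baseline value; ANCOVA would be more precise at almost no cost

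*Protocol article*

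**What the plan says.** Two parts of the Protocol article bear on this.

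*Measurement.* Study design states: "All outcomes will be evaluated at the start of treatment and 4 weeks later". Secondary outcomes states: "All the primary and secondary outcomes will be assessed before and 1 week after treatment". Table 1 places laboratory tests, EMG, JOA and MPQ at week −1, before allocation, and again at week 4. These places disagree on when the post-treatment measurement falls, but all agree that each outcome has a pre-treatment value.

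*Analysis.* The Statistical analysis section gives this rule for continuous data: "For continuous variables, mean ± SD will be recorded by using ANOVA test if they were normally distributed". Where normality fails, it replaces the comparison of means by the rank-based Kruskal–Wallis test. Tukey and Bonferroni procedures are named for multiple comparisons. The section names no covariate, ANCOVA, change score or group-by-time model. Its only mention of adjustment concerns imputation of missing data. It also does not say which quantity the ANOVA is applied to.

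Allocation describes random-number assignment "with a ratio of 1:1:1" and mentions no stratification on a baseline value.

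**The concern.** When the same outcome is measured before and after treatment, the baseline value predicts part of the post-treatment value. A comparison of post-treatment means leaves that predictable part in the error term. A comparison of changes removes a fixed amount of it, whatever the correlation. ANCOVA removes the right amount.

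Two things are at stake. The first is precision, in a trial of 28 per arm whose questions are the pairwise ones, Qigong against MCE and Qigong against celecoxib. The second is the handling of chance baseline differences, which are not small in arms of this size and which the described allocation does nothing to balance. The fallback for non-normal data, Kruskal–Wallis, has no place for a covariate at all.

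**Working it through.** **Inputs.** From Sample size: "By utilizing a two-sided 0.05 level *t*-test with >95% power and assuming a 10% dropout rate" and "To detect a target effect size of 0.44 (GPower 3.1) with 28 participants in each group, a sample size of 84 participants is needed". From Allocation: 28 per arm. The baseline-to-post correlation r is not given for any outcome, so r = 0.3, 0.5 and 0.7 are assumed. The variance formulas also assume equal SD at the two time points and a common linear slope.

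**The plan's own figure.** The article does not say whether 0.44 is Cohen's f or Cohen's d.
- As f in a three-group ANOVA, the noncentrality at N = 84 is 84 × 0.44² = 16.26. With 2 and 81 degrees of freedom the power is 95.3%. This matches 84 with nothing added for dropout.
- As d in a two-sided two-sample t-test, 28 per arm gives 36.6%, and 95% power needs 136 per arm. This does not match.

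The f reading is therefore used for the main figures. With 10% dropout, 28 × 0.9 = 25.2, so about 25 complete per arm and N = 75. The noncentrality is then 75 × 0.44² = 14.52, and unadjusted power on post-treatment values is 92.7%.

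**Relative variance of a group difference** (post values = 1):
- change values: 2(1 − r)
- ANCOVA: 1 − r²
- change minus ANCOVA: 2(1 − r) − (1 − r²) = (1 − r)², which is positive for every r below 1
- change minus post values: 1 − 2r, so change is worse than post values when r is below 0.5

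**ANCOVA power.** Replace f by f/√(1 − r²), so the noncentrality is 14.52/(1 − r²), with 71 error degrees of freedom instead of 72.

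| Assumed r | Post values | Change | ANCOVA | 25 per arm under ANCOVA equals, unadjusted | Noncentrality, N = 75 | Omnibus power, N = 75 |
|---|---|---|---|---|---|---|
| none (unadjusted) | 1 | – | – | 25 | 14.52 | 92.7% |
| 0.3 | 1 | 1.4 | 0.91 | 25/0.91 = 27 | 15.96 | 94.8% |
| 0.5 | 1 | 1.0 | 0.75 | 25/0.75 = 33 | 19.36 | 97.8% |
| 0.7 | 1 | 0.6 | 0.51 | 25/0.51 = 49 | 28.47 | 99.8% |

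**If 0.44 were d instead.** Pairwise power at 25 per arm, before any multiplicity correction, goes from 33% to 36%, 42% or 57%. That power is low because of the sample-size basis, and ANCOVA does not cure it.

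**Chance baseline difference.** Between two arms of 28 the standard error is √(2/28) = 0.27 SD, with a 95% range of ±1.96 × 0.267 = ±0.52 SD. By simulation, the largest of the three pairwise differences has median 0.30 SD and exceeds 0.25 SD with probability 0.62. With post values, r times the difference carries into the contrast. For a difference of 0.30 SD that is 0.09, 0.15 or 0.21 SD at r = 0.3, 0.5 or 0.7. With change values, (1 − r) times the difference carries over in the opposite direction.

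**The case against.** The strongest case on the other side has four parts.

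1. *The text does not fix an unadjusted model on post-treatment values.* It says ANOVA, not one-way ANOVA, and leaves the dependent variable unnamed. A reader might infer that the plan ignores baseline altogether. The article does not support that: change values are not mentioned, but they are not excluded, and analysing them would use baseline. This stands. It does not remove the point, because change values are also less precise than ANCOVA at every r below 1.

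2. *Covariates may be set out in a fuller document.* An article can leave model detail to an analysis plan that is not shown. But this article does not defer the choice. It names the test for each type of data, and the test it names for non-normal data cannot take a covariate. The point is about that stated choice, not about missing detail.

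3. *Nothing is invalid.* A reader might infer that the planned comparison is biased. It is not: under randomisation, ANOVA on post values or on changes is unbiased and keeps its type I error, and its standard error already allows for chance imbalance. Only a fraction of any observed imbalance carries over. This stands in full and makes the matter one of efficiency, and of bias conditional on the imbalance that happens to occur.

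4. *The gain is assumed.* With no r in the article, the benefit may be slight; at r = 0.3 omnibus power moves by about two points. This stands too, but the price is one error degree of freedom.

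**Conclusion.** The point holds as one of precision and of an incompletely specified analysis, not of validity. Data already planned for every participant would be used less well than they could be, whether post values or changes are compared.

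The size depends on r. The variance reduction against post values is 9%, 25% or 49% at r = 0.3, 0.5 or 0.7: minor at the low end and substantial at the high end. On the f reading of 0.44 and with 10% dropout, unadjusted power falls short of the stated 95%. ANCOVA comes close to it at r = 0.3 and passes it at r = 0.5 and above. These figures rest on the assumed r, on equal variance at the two time points, and on 0.44 being Cohen's f.

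**What to change.** In Statistical analysis, make the primary analysis of each continuous outcome an ANCOVA: the post-treatment value on treatment group, with the baseline value of the same outcome as covariate. Report the adjusted Qigong–MCE and Qigong–celecoxib differences with 95% confidence intervals.

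For skewed positive outcomes, such as EMG amplitude measures and the two biomarkers, log-transform both time points and fit the same model. Keep Kruskal–Wallis as a sensitivity check. Do not log-transform muscle activation order or signed onset differences; an order or a signed quantity does not suit that transformation.

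Reconcile the post-treatment time point between Study design (4 weeks) and Secondary outcomes (1 week after treatment), so that the response variable is defined.

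The cost is a change of wording and one error degree of freedom per model. No further data or participants are needed.
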